## Abstract

**Background:**

Depression is a common psychiatric disorder characterized by a high rate of relapse and recurrence. The most commonly used strategy to prevent relapse/recurrence is maintenance treatment with antidepressant medication (mADM). Recently, it has been shown that Mindfulness-Based Cognitive Therapy (MBCT) is at least as effective as mADM in reducing the relapse/recurrence risk. However, it is not yet known whether combination treatment of MBCT and mADM is more effective than either of these treatments alone. Given the fact that most patients have a preference for either mADM or for MBCT, the aim of the present study is to answer the following questions. First, what is the effectiveness of MBCT in addition to mADM? Second, how large is the risk of relapse/recurrence in patients withdrawing from mADM after participating in MBCT, compared to those who continue to use mADM after MBCT?

**Methods/design:**

Two parallel-group, multi-center randomized controlled trials are conducted. Adult patients with a history of depression (3 or more episodes), currently either in full or partial remission and currently treated with mADM (6 months or longer) are recruited. In the first trial, we compare mADM on its own with mADM plus MBCT. In the second trial, we compare MBCT on its own, including tapering of mADM, with mADM plus MBCT. Follow-up assessments are administered at 3-month intervals for 15 months. Primary outcome is relapse/recurrence. Secondary outcomes are time to, duration and severity of relapse/recurrence, quality of life, personality, several process variables, and incremental cost-effectiveness ratio.

**Discussion:**

Taking into account patient preferences, this study will provide information about a) the clinical and cost-effectiveness of mADM only compared with mADM plus MBCT, in patients with a preference for mADM, and b) the clinical and cost-effectiveness of withdrawing from mADM after MBCT, compared with mADM plus MBCT, in patients with a preference for MBCT.

**Trial registration:**

ClinicalTrials.gov: NCT00928980

## Background

Major depressive disorder (MDD) is one of the most prevalent psychiatric disorders characterized by high relapse and/or recurrence rates. Relapse is defined as ‘a return of symptoms satisfying the full syndrome criteria for an episode that occurs during the period of remission, but before recovery’, where remission is a period in which the individual no longer meets syndrome criteria for the disorder and has no more than minimal symptoms, and recovery is being in remission for 6 months or longer; recurrence is ’ the appearance of a new episode of MDD occurring during recovery’ [1]. In a large prospective study, a recurrence rate of 85% was observed in outpatients with MDD during a follow-up period of 15 years [2]. Furthermore, the recurrence risk has been shown to increase with 16% after each successive episode [3]. Given the high psychological as well as social and economic burden associated with MDD, relapse/recurrence prevention is extremely important. The most commonly used strategy to prevent relapse/recurrence is maintenance treatment with antidepressant medication (mADM). International guidelines recommend that patients with recurrent MDD should continue mADM for at least two years after remission [4]. A meta-analysis showed that mADM reduces relapse/recurrence rates significantly compared to placebo (18% versus 41%) based on 31 randomized controlled trials with follow-up periods ranging from 6 to 36 months [5]. However, despite the established effectiveness of mADM as a preventive strategy, it has several disadvantages. First, many patients are unwilling to continue mADM for a longer period [6] and adherence is typically low [7]. Second, many patients experience disturbing side effects [8]. Moreover, many patients prefer psychological over pharmacological treatment [9]. Psychotherapeutic approaches also seem to have long-term beneficial effects, whereas effects of mADM cease after discontinuation [10]. To address the need for psychological interventions targeting relapse prevention, Segal, Williams and Teasdale developed Mindfulness-Based Cognitive Therapy (MBCT) [11]. The aim of MBCT is not to change or eliminate depressive symptoms, but rather to relate to them in a different way, i.e. with a more accepting, mild attitude. The rationale behind the MBCT program is based on an empirically supported, theoretical framework suggesting that patients with recurrent depression become more vulnerable to developing depression as cognitive reactivity increases (for a review see [12]). Cognitive reactivity refers to negative modes of thinking and behaving that are reactivated in periods of stress or low mood. It is suggested that these (automatic) negative reactions in turn, lead to a further lowering of mood, eventually turning into a depressive relapse/recurrence [13]. Cognitive reactivity is strongly related to rumination, which refers to recurrently thinking about one’s depressive symptoms and their possible causes and implications. Rumination is thought to be an important cognitive vulnerability factor for both onset and relapse/recurrence in depression [14,15]. MBCT is targeted at recognizing these cognitive and behavioral reactions to low mood or other stressful situations, and to observe these reactions with acceptance and kindness and from a wider, decentered perspective. Indeed, there is evidence that MBCT diminishes the ‘toxic’ relationship between post-treatment cognitive reactivity and depressive relapse [16] and that decreased rumination mediates the effects of MBCT [17]. Unlike cognitive reactivity and rumination, self-compassion seems to be a beneficial factor that is protective against depression. Self-compassion can be described as a combination of (a) self-kindness - being kind and understanding toward oneself in instances of pain or failure, (b) common humanity - perceiving one’s experiences as part of the larger human experience, and (c) mindfulness - holding painful thoughts and feelings in balanced awareness [18]. Evidence suggests that both self-compassion and mindfulness skills mediate the effect of MBCT on relapse/recurrence [16]. Three randomized controlled trials (RCTs) have shown that MBCT in addition to treatment as usual (TAU) significantly reduced the relapse/recurrence risk compared with TAU alone, over a period of 14 months [19-21]. In the first two trials [19,20], beneficial effects of MBCT were seen in patients with three or more past episodes, whereas no difference in relapse/recurrence percentages between MBCT and TAU was observed in patients with two past episodes (but see [22] for positive effects of MBCT in patients with one or two past episodes). Another trial has shown that MBCT’s prophylactic effect is at least equal to mADM for patients with three or more past episodes [23]. This latter finding may specifically apply to patients whose remission is unstable [24]. There is also evidence that MBCT might reduce subthreshold depressive symptoms, an important risk factor for relapse/recurrence, in patients remitted from MDD [22] and patients with current MDD [17]. A recent meta-analysis [25] showed that the overall risk ratio for relapse/recurrence after MBCT is 0.66 (a relative risk reduction of 34%) compared with TAU or placebo indicating that MBCT is indeed an effective prophylactic intervention for patients with recurrent MDD in remission. However, the prophylactic effectiveness of the *combination* of MBCT plus mADM has not yet been compared with either mADM or MBCT on their own. More specifically, MBCT has not been studied as an additional treatment in patients continuing mADM, rather than TAU, to prevent relapse/recurrence. Also, up to now we do not know if continuing mADM after MBCT has additional benefits over withdrawing from mADM after MBCT. As more and more MBCT courses are available, answering these specific questions becomes increasingly important for patients and clinicians in order to find the optimal strategy to prevent relapse/recurrence. The current study is designed to answer these questions.

### Aims

The purpose of the ‘MOMENT’ study is twofold using two separate but connected RCTs to answer the following questions: 1) “In patients who are in remission of depression, who are being prescribed mADM and who are reluctant to discontinue medical treatment, is MBCT when given as an add-on therapy superior to the continuation of medical treatment alone?” (mADM versus mADM + MBCT) and 2) “In patients who are in remission of depression who are being prescribed mADM and who are willing to try MBCT and not unwilling to discontinue medical treatment, is MBCT with a tapering off regimen of the medical treatment not inferior to MBCT in combination with continued medical treatment?” (MBCT versus mADM + MBCT). Our primary outcome is relapse and/or recurrence. Thus, the results of this study will inform patients with MDD and mental health professionals about the relapse and recurrence risks associated with the different treatment options given a certain treatment preference, and will support decision making processes regarding these options. In addition to these primary aims, we intend to examine; 3) the effect of mADM versus mADM + MBCT on the time to, number, duration and severity of relapse/recurrence, quality of life, and personality; 4) the effect of MBCT versus mADM + MBCT on the time to number, duration and severity of relapse/recurrence, quality of life, and personality; 5) several process variables such as MBCT adherence, rumination, cognitive reactivity, mindfulness skills, and self-compassion as possible mechanisms underlying the clinical effectiveness of MBCT; 6) the cost-effectiveness of mADM versus mADM + MBCT and 7) the cost-effectiveness of MBCT versus mADM + MBCT.

## Methods

### Design

Originally the study was designed as a single trial, randomizing patients who are in remission of depression over [a] continuation of medical treatment, [b] switching to MBCT, or [c] MBCT as an add-on to medical treatment. This protocol was approved by our ethical review board (CMO Arnhem-Nijmegen) and registered under number 2008/242. However, inclusion of patients was hampered by the fact that many patients turned out to have a strong treatment preference: some patients were eager to start with MBCT and other patients were reluctant to discontinue medical treatment. Continuing the trial as a trial with preference arms would have resulted in a substantial proportion of patients who would not have been randomly allocated to treatment, introducing a potential serious bias. We therefore decided to conduct two separate RCTs, one with patients who are reluctant to discontinue medical treatment, and one with patients who are particularly eager to try MBCT and at least not unwilling to discontinue medical treatment. In the former, patients are randomly allocated to either continuation of medical treatment, or continuation of medical treatment with MBCT as an add-on therapy (a parallel-group, randomized controlled superiority trial). In the latter, patients are allocated to either MBCT while continuing medical treatment, or to MBCT in combination with a tapering-off regimen of the medical treatment (a parallel-group, randomized controlled non-inferiority trial). In this way, we take optimal account of the patient preferences and the study population will be as representative as possible of patients seen in routine clinical practice. The change in protocol has been approved by the Medical Ethics Committee Arnhem-Nijmegen (20-02-2011). Here, we report the design of the two trials. See Figure 1 for a flow chart of the recruitment and study procedure.

**Figure 1 F1:**
[figure not shown]
Flow chart of the recruitment and study procedure.

### Sample size

#### *Trial 1: mADM* versus *mADM + MBCT*

For trial 1 we need to recruit 96 participants (n = 48 per group) in order to demonstrate a difference of 25% in relapse/recurrence rates between mADM and mADM + MBCT, with a power of 80% (alpha 0.05, one-sided). This calculation is based on earlier studies reporting relapse/recurrence percentages of 60% in the mADM group [23] and approximately 38% in the MBCT plus TAU group [25]. Because our trial investigates MBCT plus mADM rather than MBCT plus TAU, we expect an even lower relapse/recurrence percentage (about 35%) in the combination group. Our expected difference is therefore 60% (mADM) minus 35% (mADM + MBCT) resulting in 25%.

#### *Trial 2: MBCT* versus *mADM + MBCT*

The sample size of trial 2 is based on the principle of non-inferiority. According to the Draft Guidance for Industry Non-Inferiority Clinical Trials of the US Food and Drug Administration [26] non-inferiority should be demonstrated by comparing the new, experimental treatment with an established efficacious treatment. In the case of relapse prevention in depression, this established treatment is mADM. However, since a head to head comparison of MBCT with mADM is complicated due to our design, we compare MBCT with the combination therapy (mADM + MBCT). We reasoned that the difference in relapse/recurrence between MBCT and mADM + MBCT should not be larger than the difference between the established treatment (mADM) and mADM + MBCT, which is expected to be approximately 25%. Therefore, we chose a non-inferiority margin of 25%. Based on this assumption, the sample size needed in this non-inferiority trial is 280 in total (n = 140 per group) with a power of 80% (alpha 0.05, one-sided).

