### Statistical analysis

#### Primary analyses

Our primary analyses will be based on intention-to-treat. Subsequently per-protocol analyses will be conducted. All analyses will be performed with and without covariates (i.e. the stratification factors research centre, depressive symptoms at baseline, and number of depressive episodes in the past, as well as other variables that might inadvertently be unevenly distributed over the conditions at baseline). *Trial 1: mADM* versus *mADM + MBCT.* The primary outcome measure will be relapse and/or recurrence meeting DSM-IV criteria for a major depressive episode during the 15-month study period. Relapse/recurrence rates will be compared with a Chi-square test. *Trial 2: MBCT* versus *mADM + MBCT.* The primary outcome measure will be relapse and/or recurrence meeting DSM-IV criteria for a major depressive episode during the 15-month study period. Relapse/recurrence rates will be compared with a General Linear Model using a binomial family with an identity link. We will use the confidence interval (one-sided) of the difference in relapse/recurrence between the two conditions (MBCT versus mADM + MBCT): if a difference of 25% can be excluded, then we will conclude non-inferiority of MBCT in comparison with mADM.

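### Trial 2's 280 patients do not follow from the printed 25-point margin, one-sided alpha 0.05 and 80% power; an assumption is unstated or a figure needs correcting

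*Protocol article*

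**What the plan says.** The sample size section for trial 2 reasons that MBCT with tapering should not fall further behind mADM + MBCT than mADM alone is expected to, about 25 points. It continues: "Therefore, we chose a non-inferiority margin of 25" per cent. On that basis, it says, "the sample size needed in this non-inferiority trial is 280 in total (n = 140 per group) with a power of 80" per cent, at one-sided alpha 0.05. It prints no expected relapse rates, true difference or dropout allowance for this trial.

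The Primary analyses section applies the same threshold to a one-sided confidence limit for the risk difference: "if a difference of 25% can be excluded, then we will conclude non-inferiority of MBCT in comparison with mADM".

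The only relapse rates in the article's sample size section are those given for trial 1: "relapse/recurrence percentages of 60% in the mADM group", "approximately 38% in the MBCT plus TAU group", and for the combination, "we expect an even lower relapse/recurrence percentage (about 35%) in the combination group".

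**The concern.** A 25-point margin on a risk difference is wide, and at 80% power it normally needs a small trial. Trial 1 is planned to detect a difference of the same size with the same alpha and power, and it needs only 48 per group. Trial 2 is given 140 per group, almost three times as many, without explanation.

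The margin is the threshold on which trial 2's conclusion rests, so readers need to know that the trial was sized for the threshold it will apply. If the two arms are assumed equal, the printed inputs justify only about a third of the planned patients. If a materially worse outcome after tapering was assumed instead, that expectation matters for interpreting the trial and should be visible.

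**Working it through.** **Inputs.** Margin M = 0.25, one-sided alpha 0.05, power 80% and 140 per group come from the trial 2 sample size section. The rates 60%, 38% and 35% come from the trial 1 section. My assumptions are no dropout and, in the base case, a true difference of zero.

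**Check of the method on trial 1.** For 60% against 35%, one-sided 0.05 and 80% power:
- unpooled variance: (1.645 + 0.842)² × (0.60×0.40 + 0.35×0.65) / 0.25² = 6.183 × 0.4675 / 0.0625 = 46.2, so 47 per group
- pooled variance: 49 per group

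The article states 48, so trial 1 reproduces.

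**Formula for trial 2.** With pc the relapse risk on mADM + MBCT and pt the risk on MBCT with tapering,

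n per group = (z₀.₉₅ + z₀.₈₀)² × [pc(1−pc) + pt(1−pt)] / [M − (pt − pc)]²

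**Results at M = 0.25**

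| pc | pt | Calculation | n per group | Total |
|---|---|---|---|---|
| 35% | 35% | 6.183 × 0.455 / 0.0625 = 45.01 | 46 | 92 |
| 38% | 38% | 6.183 × 0.4712 / 0.0625 = 46.6 | 47 | 94 |
| 60% | 60% | 6.183 × 0.48 / 0.0625 = 47.5 | 48 | 96 |
| 50% | 50% | 6.183 × 0.50 / 0.0625 = 49.5 | 50 | 100 |
| 35% | 38% | 6.183 × 0.4631 / 0.0484 = 59.2 | 60 | 120 |

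The variance is largest at 50%, so no common risk needs more than 50 per group.

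**Power at 140 per group, M = 0.25.** Power = Φ{[M − (pt − pc)] / SE − 1.645}, with SE = √{[pc(1−pc) + pt(1−pt)] / 140}.
- 35% in both arms: SE 0.0570, power 99.7%
- 50% in both arms: SE 0.0598, power 99.4%
- 35% against 38%: SE 0.0575, 0.22 / 0.0575 = 3.83, power 98.5%

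**Usual explanations tried**
- One-sided alpha 0.025: 58 to 63 per group with equal risks, 76 with 35% against 38%.
- One-sided alpha 0.025 with 90% power, equal risks: 77 to 85 per group.
- Continuity correction, equal risks: 53 to 58 per group.
- Dropout: with equal risks, about 64% to 67% would have to be lost for 140 to be the inflated figure.

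None of these accounts for 140.

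**What does give 140 per group**
- M = 0.25 with a true disadvantage for tapering. 35% against 45% gives 131, 35% against 46% gives 151, and 35% against 45.5% gives 6.183 × 0.4755 / 0.145² = 139.8, so 140.
- No true difference with a smaller margin. At M = 0.15 the need is 126 per group at 35% and 138 at 50%. Solving for the margin at exactly 140 per group and 80% power gives 14.2 points at 35% and 14.9 at 50%.

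**The case against.** The strongest reply is that a non-inferiority sample size depends on an assumed true difference as well as on the margin, alpha and power. This is a condensed journal article, and it may have left that assumption to the full protocol. An expected disadvantage of about 10.5 points reproduces 280 with the margin and power exactly as printed. The direction at least fits the trial 1 section, which expects less relapse on MBCT plus mADM than was reported for MBCT plus TAU. This stands. A reader might infer that the margin or the power must be wrong, but the document does not support that, because an omitted assumption is a third explanation.

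A reader might also infer that the true margin was 15 points. The documents do not support this either. No section mentions 15 points. The 25 points are derived from the expected 60% minus 35%, and the analysis section repeats them. The fit is also loose: at 35% in both arms a 15-point margin gives 83.8% power at 140 per group, and at 35% against 38% it gives about 67% and would need 199 per group.

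Finally, if the arms are equal, the trial is larger than a 25-point margin needs. That does not inflate the error rate or invalidate the confidence-interval test.

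The reply does not remove the discrepancy. The article presents 280 as resting on the margin alone, and it prints the expected rates for trial 1. For trial 2 it states a derivation that does not hold as written.

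**Conclusion.** The concern holds as a failure of the stated calculation to reproduce. The stated 140 per group is about three times the 46 to 50 needed with equal risks, and 2.3 times (140/60) the 60 needed with 35% against 38%. The stated power of 80% would be about 98.5% to 99.7% in those cases. These figures rest on the unpooled risk-difference formula, no dropout, and true differences of zero or three points; the 35% and 38% are borrowed from trial 1.

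The document cannot show whether the cause is an unstated disadvantage of about 10.5 points, a different margin at the time of the calculation, or a misstated power. It does not show that the 25-point margin is an error.

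**What to change.** Keep 280 patients, and keep the 25-point margin in both the sample size and the Primary analyses sections, unless the sponsor's own records show that another margin was used. Then correct the trial 2 sample size section in one of two ways:

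- **Restate the power** that 140 per group gives for a 25-point margin, with the rates assumed: about 98.5% at 35% against 38%, above 99% at equal risks.
- **State the missing assumptions**: the expected relapse rate in each arm, the true difference and any dropout allowance that together yield 140 per group at 80% power.

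The margin should not be changed to 15 points to match the arithmetic. That would replace the primary decision rule and break its stated rationale.

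The cost is a check of the original calculation and a few sentences in one section. No extra patients are needed, and the analysis does not change.

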### Participants

The study protocol has been approved by the Medical Ethics Committee Arnhem-Nijmegen (nr. 2008/242) for all participating sites. Local Ethics Committees approved local feasibility. Patients are included in the study only after written informed consent has been obtained. Participation is completely voluntary and patients can withdraw from the study and/or treatment at any time without having to give a reason for withdrawal and without consequences for their treatment options. Suspected serious adverse events are recorded and reported to the Medical Ethics Committee Arnhem-Nijmegen. Patients are recruited from nine centers across the Netherlands: Department of Psychiatry, Radboud University Nijmegen Medical Center; Department of Psychiatry, Academic Medical Center, Amsterdam; GGZ inGeest, partner VU University Medical Center, Amsterdam; Pro Persona Ede, Tiel and Arnhem; Parnassia Bavo Psychiatric Institute, The Hague; PsyQ Psycho Medical Programmes, The Hague; Leiden University Medical Center Leiden and GGZ Rivierduinen, Leiden and Lisse; GGZ Centraal, Amersfoort; and GGZ Noord-Holland-Noord, Alkmaar. Recruitment was done via referrals from mental health professionals and by media advertisements.

#### Inclusion criteria

Inclusion criteria for the MOMENT study are: a) MDD with a history of at least three depressive episodes according to the Diagnostic and Statistical Manual of Mental Disorders - 4th edition (DSM-IV [27]) using the Structured Clinical Interview for DSM disorders I (SCID-I [28]); b) treated with a stable dose of mADM over the last 6 months or longer; c) currently either in full or partial remission. Full remission is defined in our study as not currently meeting the criteria for a depressive episode assessed by the SCID and having a score of ≤ 11 on the Inventory of Depressive Symptomatology – Clinician rating (IDS-C_30_[29]). Partial remission is defined as not currently meeting the criteria for a depressive episode and having an IDS-C score > 11. The cut-off point of ≤ 11 > on the IDS-C corresponds to a Hamilton Rating Scale for Depression score of 8 which is often used as a cut-off score for remission [30]; d) native Dutch speaking.

